#### Monitoring and data management

The trial will take place at the Medical Research Council’s Cognition and Brain Sciences Unit in Cambridge, England. As a Phase II trial, a data-management committee was considered unnecessary and the trial team is therefore responsible for monitoring and data management. Data will be monitored for completeness, consistency, and plausibility using spot checks and plausibility checks carried out by the trial statistician. The trial lead ([name]), statistician ([name]) and coordinator ([name]) will have full access to the final trial dataset. The study data will be reported in line with the current CONSORT recommendations
[39].

#### Safety aspects

Adverse events refer to unwanted medical events (for example, worsening symptoms) occurring throughout the trial, regardless of whether they are causally related to the trial procedures. Adverse events are managed in line with UK MRC protocols, and in the unlikely case of an adverse event, it will be documented appropriately. Precautions have been taken to reduce the likelihood of adverse events occurring; for example, patients who are acutely suicidal or at high risk of harm do not meet study inclusion criteria. The interventions are delivered by clinical psychologists experienced in the management of risk and in the treatment of chronic, recurrent, and severe depression. In the case of any adverse events, participation in the trial will be discontinued. The trial is underwritten by the UK MRC in case any individual suffers harm or requires post-trial care.

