### Measures

#### Primary outcomes

The primary outcome measure will be depressive symptoms at 3-month follow-up using the well-established, psychometrically sound self-report measure, the Beck Depression Inventory II (BDI-II)
[31].

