#### Data collection

Outcome data will be collected on site at three assessment points (baseline, post-treatment, and 3-month follow-up). Outcome data on all participants who are randomised will be collected if possible and with appropriate consent. At 6-month follow-up, participants from the MEST arm will be contacted by phone and administered the Longitudinal Interval Follow-Up Evaluation to ascertain depression-free days (a form of the SCID-IV), and will be asked to complete the BDI-II electronically. Memory specificity and the full process battery will not be administered at the 6-month follow-up. Data will be stored securely at this site under the management of the trial coordinator ([name]). Spot checks on data entry will be performed to promote data quality.

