#### Statistical analysis plan

Initial analyses of the primary and secondary outcomes will be conducted by the trial statistician, following CONSORT standards (there are no planned interim analyses). Multiple imputation will be used to handle missing data. Initial analyses will be conducted on an intention-to-treat basis, with subsequent analyses being per protocol. Mixed model analyses of variance (ANOVAs) will be used to compare groups at the four assessment points - baseline, post-intervention, 3-month follow-up, and 6-month follow-up on primary and secondary outcomes, as appropriate. Baseline levels on relevant measures will be included as covariates, as appropriate. Mediational analyses following the Kraemer recommendations
[34] will investigate hypothesised mechanisms of change across the trial arms.

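### Ending trial participation for any adverse event, with worsening symptoms counted as one, conflicts with collecting outcomes on everyone randomised and can make the 3-month BDI-II missing because of itself

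*Protocol article*

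**What the plan says.** Safety aspects defines adverse events as "unwanted medical events (for example, worsening symptoms) occurring throughout the trial, regardless of whether they are causally related to the trial procedures". No severity threshold is given. The same section then says "In the case of any adverse events, participation in the trial will be discontinued". The object of that sentence is the trial, not the treatment.

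Three other sections bear on this:

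- Primary outcomes: "The primary outcome measure will be depressive symptoms at 3-month follow-up", measured by the BDI-II.
- Data collection: "Outcome data on all participants who are randomised will be collected if possible and with appropriate consent". On-site assessments are at baseline, post-treatment and 3 months. No BDI-II is specified at the time of an adverse event.
- Statistical analysis plan: "Initial analyses will be conducted on an intention-to-treat basis, with subsequent analyses being per protocol". Also, "Multiple imputation will be used to handle missing data".

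Nowhere does the article say that someone discontinued after an adverse event is still assessed.

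**The concern.** Everyone enrolled is in a current major depressive episode, so some will get worse during the five weeks of sessions or the following three months. Under the Safety aspects wording, that worsening is an adverse event and ends participation. The person's later BDI-II scores are then missing because depression worsened, which is the event the primary outcome is meant to register.

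Multiple imputation in its usual form assumes that, given the recorded data, those removed resemble those who stayed. If the worsening was never recorded, the imputed scores are too low. Both arm means then look better than they are, and the between-arm difference is distorted if one arm loses more people this way than the other.

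This matters because the Power analysis and sample size section says the trial's purpose is to judge efficacy, feasibility and acceptability and to supply effect estimates for sizing a later trial. Scores that were not collected cannot be recovered at analysis.

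**Working it through.** **1. The passages side by side.**

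| Section | What it requires after a participant worsens |
|---|---|
| Safety aspects | Participation in the trial ends |
| Data collection | Outcomes still sought, if possible and with consent |
| Statistical analysis plan | Participant analysed as randomised, with missing values imputed |

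The first two rows cannot both be followed. The third can still be carried out formally, but on imputed values.

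**2. The plan's own figure.** Allowing 20% attrition from 30 per arm leaves 30 × (1 − 0.20) = 24, as stated. The allowance is 6 people per arm. The article gives no SD, effect size or event rate, so everything below rests on assumptions.

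**3. Assumed inputs.** Baseline BDI-II mean 28, SD 10, entry above 13 (the entry limit is from Participants and recruitment). Correlations: baseline with post-treatment 0.6, baseline with 3 months 0.5, post-treatment with 3 months 0.75. Mean falls in ES of 4 points at post-treatment and 5 at 3 months. Removal when the score rises by at least 3, 5 or 8 points during treatment. The 3-month score of those removed is imputed by regression within arm. The results are large-sample simulation values (about a million or more per arm).

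**4. Worsening not recorded (imputation from baseline only), ES arm.**

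| Rise that triggers removal | ES removed | ES 3-month mean, true | Imputed | Error |
|---|---|---|---|---|
| 3 points | 19.4% | 23.7 | 21.8 | −1.9 |
| 5 points | 13.7% | 23.7 | 22.3 | −1.4 |
| 8 points | 7.5% | 23.7 | 22.9 | −0.8 |

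In an arm of 30, that is 30 × 0.075 = 2.3 to 30 × 0.194 = 5.8 people, against the allowance of 6.

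**5. Worsening not recorded, between-arm difference (MEST minus ES).** Each range covers triggers of 3 to 8 points.

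| True difference at 3 months | MEST advantage at post-treatment | Estimate | Shrinkage |
|---|---|---|---|
| −5.0 | 5 points | −3.9 to −4.5 | about 11% to 21% |
| −5.0 | 3 points | −4.3 to −4.6 | about 7% to 14% |
| −4.0 | 4 points | −3.1 to −3.5 | about 12% to 22% |
| −5.0 | 0 points | −5.0 | none |

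Shrinkage is 1 − estimate/true on unrounded values. In the last row removal is equal in the two arms, so the contrast is unbiased, although both arm means are still too low by the amounts in step 4.

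**6. Worsening recorded.** The same model with the post-treatment BDI-II added to the imputation gives an ES mean of 23.7 (true 23.7) and differences of −5.0 (true −5.0) and −4.0 (true −4.0). The bias is zero in every scenario, because removal then depends only on recorded scores.

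**7. A second set of assumptions.** All correlations 0.6, ES mean change 0 or −5, removal on any rise or on a rise above 5 points, true difference −5. If removal comes before the post-treatment visit, the estimate is −4.5 to −4.8. If the worsening comes after that visit and removal precedes the 3-month visit, it is −2.4 to −4.0. If the worsening is recorded at the post-treatment visit, it is about −5.0. Timing and recording therefore matter more than the exact trigger.

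**The case against.** The strongest reply is that the bias is conditional. BDI-II is collected at post-treatment, and someone whose worsening shows in that score before removal causes no bias once the score enters the imputation model. Step 6 confirms this, and it stands. A reader might infer that the rule biases the 3-month comparison outright. The documents do not support that: bias needs removal before a scheduled score records the worsening, and the contrast also needs unequal removal between arms.

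It may also be inferred that the rule makes intention-to-treat impossible. It does not. The plan pairs intention-to-treat with multiple imputation, so those removed can be analysed as randomised. The direct conflict is with Data collection.

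The 3-to-8-point trigger is an assumption. Safety aspects sets no BDI-II threshold and describes an adverse event as improbable, which suggests that few removals were expected. That expectation sits uneasily with a definition that covers any worsening in recurrent depression, but the removal percentages above remain assumptions.

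The qualifier in Data collection, that data are gathered if possible and with consent, softens the conflict but does not remove it, since nothing says that follow-up continues once participation has ended.

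It would be tempting to add that harms after a first event go uncounted. That is inference: the section defines events as occurring throughout the trial and says they will be documented, under management protocols that are not shown. Nor is the lack of a delta-adjusted analysis a fault, since an article commonly leaves such detail to the analysis plan.

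Finally, the shift in the contrast under the main assumptions, about 0.4 to 1.1 points, is small beside the standard error of the difference: 10 × √(2/24) = 2.9 at 24 per arm. That limits its effect on inference. It does not make a systematic error harmless when the estimate is to guide the size of a later trial.

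**Conclusion.** The point holds as a conflict between stated rules that carries a conditional risk of bias. Applied literally, the Safety aspects rule stops follow-up for a reason bound up with the primary outcome, contrary to Data collection, and leaves the intention-to-treat result resting on imputation for those removed.

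If the worsening is not captured in a scheduled BDI-II first, imputation under missing at random would be expected to make 3-month arm means too favourable. It would distort the difference as well if removal differs by arm.

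The size cannot be derived from the documents. Under the main assumptions (SD 10, unrecorded rise of 3 to 8 points) the ES mean is 0.8 to 1.9 points too low, and a true difference of 4 to 5 points shrinks by about 7% to 22% when MEST lowers post-treatment scores by 3 to 5 points. Other assumptions, notably worsening after the post-treatment visit, give larger errors. Recorded worsening gives none.

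**What to change.** Reconcile Safety aspects with Data collection and the Statistical analysis plan:

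- State separately what discontinuing the intervention means and what discontinuing outcome collection means.
- State that post-treatment and 3-month BDI-II, diagnostic and safety assessments are still sought, with consent, from everyone randomised, including those who stop after an adverse event. Which events end the intervention stays a clinical decision and is not judged here.
- Include the post-treatment BDI-II in the imputation model for the 3-month score.
- Optionally, add a delta-adjusted sensitivity analysis for people lost after worsening.

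The cost is a short amendment and assessments already planned for all 60 participants. The optional analysis needs no further data.

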#### Ethical approval and protocol amendments

This project has received ethical approval from the UK National Research Ethics Committee (East of England, 11/H0305/1). The study will be conducted within appropriate UK MRC, National Health Service and professional ethical guidelines, ensuring that Good Clinical Practice procedures are adhered to at all times. Protocol amendments will be circulated to the ethics, research and development, and trial team. Relevant adjustments will be made to any published protocol.

#### Confidentiality

All participants will give written informed consent prior to being assessed for eligibility of the study. To maintain confidentiality, all participants are given a trial number so that personally identifying information is not linked to assessment or trial information.

#### Dissemination policy

There are no publication restrictions, and findings will be disseminated broadly to participants, healthcare professionals, the public, and other relevant groups.

## Discussion

According to the World Health Organisation
[1], depression is major global burden of disease and, by 2020, will be the second leading cause of world disability. Depression affects people in all communities across the world, making it a matter of global concern from health, social and economic perspectives. Fortunately, evidence-based treatments that work such as cognitive-behavioural therapies are available. However, these treatments are not always accessible to those who need them, and the treatments themselves are expensive to deliver. There has been a growing recognition of the need to develop cost-effective interventions that can be delivered in a stepped care model, supported by a number of government initiatives (particularly in the UK). The underlying goal is to make evidence-based interventions more accessible and affordable (for example, NHS internet-based CBT, IAPT). The proposed RCT is in line with this objective.

The two pilot trials that have been conducted suggest that MEST, if efficacious in the treatment of depression, may offer a cost-effective, brief, low-intensity intervention with potential for cross-cultural application. For example, one of the pilot studies was conducted with Afghan refugees in Iran, the other in an inpatient sample in Belgium. This is of particular interest given that risk factors for depression include economic and social disadvantage
[40] and those in impoverished communities have greater difficulty accessing health care
[41]. If acceptability, feasibility, and superiority to the ES control can be demonstrated, the results from this trial will support the need for a fully powered Phase III definitive trial to examine MEST as a treatment for mild to moderately depressed individuals. We anticipate that MEST may be used as an adjunct or precursor to more comprehensive therapies such as CBT. It is possible that MEST may have utility in reducing symptoms to a level where patients are able to engage in more demanding therapies such as CBT. Results of this trial will also indicate whether there is potential for MEST to be used as a stand-alone treatment for depression. Further, we expect that the idiosyncratic nature of MEST may appeal to particular patient groups who do not wish to address emotional content. Finally, the embedded process study will enable us to better understand the mechanisms driving the therapeutic effects of the treatment.

## Trial status

Recruitment commenced in January 2014.

## Abbreviations

AMT: Autobiographical Memory Test; BDI-II: Beck Depression Inventory-II; CBT: cognitive behavioural therapy; CONSORT: consolidated standards for reporting trials; DSM: Diagnostic and Statistical Manual; ES: education and support; IAPT: Improving Access to Psychological Therapies; MEST: Memory Specificity Training; MRC: Medical Research Council; NHS: National Health Service; PTSD: post-traumatic stress disorder; RCT: randomised controlled trial; SCID-IV: Structured Clinical Interview for DSM-IV disorders.
